## Abstract

**Background:**

Mental practice as an additional cognitive therapy is getting increased attention in stroke rehabilitation. A systematic review shows some evidence that several techniques in which movements are rehearsed mentally might be effective but not enough to be certain. This trial investigates whether mental practice can contribute to a quicker and/or better recovery of stroke in two Dutch nursing homes. The objective is to investigate the therapeutic potential of mental practice embedded in daily therapy to improve individually chosen daily activities of adult stroke patients compared to therapy as usual. In addition, we will investigate prognostic variables and feasibility (process evaluation).

**Methods:**

A randomised, controlled, observer masked prospective trial will be conducted with adult stroke patients in the (sub)acute phase of stroke recovery. Over a six weeks intervention period the control group will receive multi professional therapy as usual. Patients in the experimental group will be instructed how to perform mental practice, and will receive care as usual in which mental practice is embedded in physical, occupation and speech therapy sessions. Outcome will be assessed at six weeks and six months. The primary outcome measure is the patient-perceived effect on performance of daily activities as assessed by an 11-point Likert Scale. Secondary outcomes are: Motricity Index, Nine Hole Peg Test, Barthel Index, Timed up and Go, 10 metres walking test, Rivermead Mobility Index. A sample size of the patients group and all therapists will be interviewed on their opinion of the experimental program to assess feasibility. All patients are asked to keep a log to determine unguided training intensity.

**Discussion:**

Advantages and disadvantages of several aspects of the chosen design are discussed.

**Trial registration:**

ISRCTN27582267

## Background

Stroke is a major health problem, which is likely to increase due to aging [1-3]. Patients are often confronted with disabilities on a physical, cognitive, social and/or communicative level. Rehabilitation of stroke patients is a time consuming process in which patients and caregivers have to learn new skills. In the Netherlands about 5,3 billion Euro are spend on rehabilitation of patients with cardiovascular diseases of which 1,5 billion is spend in nursing homes each year [4].

While it is reasonably established that the overall process of rehabilitation is effective, there is little evidence to support many specific rehabilitation therapeutic techniques [3,5]. Currently it seems that task orientated practice (i.e. practising an activity of relevance) is probably the most effective single therapeutic technique [6]. This is not dissimilar to the situation in sport where practice is the bedrock of improving skills. Indeed improving any skilled motor activity seems to depend upon continuing practice. It is perhaps this similarity that has lead to using mental practice, a technique from sports, in neurological rehabilitation.

The use of mental practice or motor imagery is well established in sports [7-12]. The principle is simple: a person imagines himself undertaking a skilled movement without actually doing the movement. It is a cognitive ability which is often used (un)consciously by all of us. Many therapists report that they use imagery in their therapy sessions already, but not systematically. They just ask the patient to imagine moving in a different way. Recently the use of mental practice has been subject to systematic research in neurological rehabilitation [13]. Although many aspects of mental practice still remain unclear, it does seem to be a promising addition to the therapy, based on best evidence. Further research into mental practice is needed, particularly where it is embedded into normal rehabilitation services.

In the Netherlands, nursing homes provide a substantial amount of stroke care although most research is restricted to academic hospitals and rehabilitation centres [14]. Consequently, more stroke research should take place in nursing homes.

The overall aim of the proposed research project is to investigate systematically the therapeutic potential of mental practice embedded in daily rehabilitation therapy on the improvement of daily activities of adult stroke patients compared to therapy as usual.

The first additional research question is which prognostic variables or patient characteristics are associated with a positive outcome in the experimental subgroup.

The second additional research question investigates the feasibility of the mental practice-based therapy as judged by the patients and therapists.

This paper reports on preliminary work, and explains the choices made in the final study design, which has been approved by the medical ethical committee of the Atrium Medical Centre & Maasland Hospital in Heerlen, The Netherlands.

### Background work

A full systematic review of previous evaluative research on mental practice was completed and has been published [13]. It showed some evidence suggesting that mental practice in stroke rehabilitation might work. However, the evidence still is weak. Furthermore, there is no consistency about or clarity on:

- the nature of the intervention itself (what was actually done?)

- the timing after stroke (when should patients be given mental practice?)

- control (what should be the control intervention?)

Consequently, we felt it important to set up a larger study. The review also highlighted several important issues to be considered in that:

- knowing what patients are doing during imagery [15],

- knowing whether patients are using mental practice [15],

- knowing what mental images of a movement the patient had [16],

- defining the core of mental practice [17],

- determining practicality in the commonest stroke rehabilitation setting (nursing homes in the Netherlands),

- determining what features predict success or failure.

These issues will be discussed also in this article.

A multi-centre, prospective, parallel-group, randomized, controlled, observer masked trial (RCT) will be conducted over a two year period (mid 2007-mid 2009) involving clinically diagnosed adult stroke patients, complying with all normal research governance procedures.

## Methods/Design

After recruitment of participants, a baseline measurement will occur (T0) followed by random assignment to either the control or experimental group. Effects of the interventions will be measured directly after the six weeks intervention period (T1) and six months after start of the intervention period (T2). Outcome measures will cover activities. Brain activity will be assessed with quantitative electroencephalography. An outline of the study design is given in figure 1.

**Figure 1 F1:**
[figure not shown]
Outline of study design. T-1 = 1–4 days before baseline. T0 = baseline. T1 = 6 weeks. T2 = 6 months.

### Study population

Seventy stroke patients will be recruited in two nursing homes by the treating physicians or other staff. There are no data available concerning ability to benefit from mental practice, and so only practical factors affect inclusion and exclusion – can the person give consent and understand the instructions?

Patients entering the RCT have to meet following inclusion criteria:

a) Clinically diagnosed adult stroke patient. In nursing homes, most of the stroke patients will be elder (> 60 years old);

b) Sufficient cognitive level and communication skills to engage in mental practice; this is a clinical judgement. Patients need to be able to follow simple instructions;

c) Between two and 10 weeks of stroke onset.

### Exclusion criteria

d) Severe additional impairments prior to stroke causing persistent disability, like rheumatic diseases, orthopaedic problems after fall.

### Sample size calculation

The calculation of the sample size is based on the primary outcome measure, perceived improvement of daily activities, like 'drinking out of a cup' and 'walking', as assessed by an 11 point Likert scale. Although arbitrary, the calculation of the sample size is based on following expectations: For us a 20% difference between the two groups in this outcome measure would be a reasonable change to aim for which means a 2.2 point change on the Numeric Rating Scale (μ1 = 2.2). There is no literature available on the standard deviation in a stroke population but in other populations the standard deviation on numerical rating scales is somewhere between 1.5 and 3.0. In this sample size calculation we will use a standard deviation of 2.25 (σ = 2.25). The power (the ability to detect a true difference in outcome) of this study is set at 90% (β = 0.10). The level of significance (likelihood of detecting a treatment effect when no effect exists) is set at 5% (α = 0.05). The power and the level of significance are generally chosen by convention.

The sample size calculation formula used for measuring the difference between two unpaired samples is: N1 = N2 = (z_1-β _+ z_1-α/2_)^2 ^* ((σ_1_^2 ^+ σ_2 _^2^)/(μ_1 _- μ_2_)^2^)

This would mean that we would need to have 19 patients in each group assuming a 50:50 random allocation. The goal of this study is to have 35 patients in each group to allow for drop-outs, loss to follow-up and uncertainty in the power calculation. A sample size of n = 70 seems realistically achievable over a 2 year period. Two nursing homes participate in this study: Klevarie nursing home (Maastricht) assesses about 200 new stroke patients each year. nursing home St. Camillus (Roermond) treats another 70 patients each year. We estimate that 40% of all treated stroke patients will be able to participate in the study, but not all will want to. If an added value of the experimental intervention can not be found in 70 patients the clinical relevance of a mental practice-based therapy should be questioned.

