### Main study parameter/endpoint

It is hypothesised that mental practice has the most effects on the movement that is actually mentally rehearsed [9,18,25,26]. Improvement of these activities should therefore be assessed. To measure if mental practice improves the performance of activities in the experimental group more than in the control group, an 11-point Likert scale will be used:

▪11 point Likert scale assesses the performance of the activities 'drinking' and 'walking' ranging from 10 ('excellent') to 0 ('poor') as perceived by the patient and the therapist. The physiotherapist and the occupational therapist will each score another task, which may be individually chosen and scored on the 11 point Likert scale. If the participant is treated for swallowing problems and/or motor problems due to a facial paresis by a speech therapist, he himself and the speech therapist will score motor actions within these two domains on perceived performance.

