### Withdrawal of individual participants

Participants can leave the study at any time for any reason if they wish to do so without any consequences. If reasons are given they will be recorded. The investigator can decide to withdraw a subject from the study for urgent medical reasons. We allowed for a 20% drop out in the size calculation.

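### The protocol's own sample size formula and inputs give 22 patients per group, not the stated 19; the recruitment target of 35 per group still covers the corrected figure

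*Protocol article*

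**What the plan says.** All the planning inputs are in the Sample size calculation section of the protocol article. The target difference is described as 20% of the outcome measure, "which means a 2.2 point change on the Numeric Rating Scale (μ1 = 2.2"). Power "of this study is set at 90% (β = 0.10") and the significance level "is set at 5% (α = 0.05"). The standard deviation is 2.25, taken from a range of 1.5 to 3.0 reported in other populations. The formula begins "N1 = N2 = (z_1-β _+ z_1-α/2_)^2" and multiplies that term by the sum of the two variances over the squared difference in means. The result is reported as: "This would mean that we would need to have 19 patients in each group assuming a 50:50 random allocation".

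The section then sets a goal of 35 per group, 70 in total, to cover drop-outs, loss to follow-up and uncertainty in the calculation. Withdrawal of individual participants adds: "We allowed for a 20% drop out in the size calculation". Main study parameter/endpoint defines the 11-point scale as running from 0 to 10. The Sample size calculation section closes by saying that if 70 patients show no added value, the clinical relevance of the therapy should be questioned.

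**The concern.** A formula, its complete inputs and its output are all printed together, and the output does not follow from the inputs. A reader who relies on 19 will believe that this many evaluable patients per group gives 90% power, and that 35 per group is nearly double what is needed.

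There is also a smaller mismatch. The difference is labelled as 20% and given as 2.2 points. That is 20% of the 11 response categories, but the scale spans 10 points.

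These figures matter beyond tidiness because the section uses the size of the trial to say how a null result should be read.

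**Working it through.** **Inputs** (Sample size calculation section unless noted)

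- Two-sided α = 0.05: z(0.975) = 1.9600
- Power 90%: z(0.90) = 1.2816
- σ1 = σ2 = 2.25, so σ1² + σ2² = 10.125
- Difference 2.2, squared = 4.84
- Stated result: 19 per group; recruitment goal: 35 per group
- Drop-out 20% (Withdrawal of individual participants)

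**Step 1: the protocol's own formula**

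N = (1.2816 + 1.9600)² × 10.125 / 4.84 = 10.507 × 2.0919 = 21.98, so 22 per group. The exact two-sided t-test needs 23. The stated 19 is not reproduced.

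**Step 2: what 19 per group delivers**

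Standard error of the difference = 2.25 × √(2/19) = 0.730. Then 2.2 / 0.730 = 3.014, and power = Φ(3.014 − 1.960) = 85.4%. By noncentral t it is 83.5%.

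**Step 3: conventions that might give 19** (difference 2.2, SD 2.25)

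| Convention | Unrounded | Normal n | t-test n |
|---|---|---|---|
| Two-sided 5%, 90% power (as printed) | 21.98 | 22 | 23 |
| Two-sided 5%, 85% power | 18.78 | 19 | 20 |
| Two-sided 5%, 80% power | 16.42 | 17 | 18 |
| One-sided 5%, 90% power | 17.92 | 18 | 19 |

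A one-sided 5% t-test at 90% power gives exactly 19 (90.5% power at 19, 89.1% at 18). A two-sided normal calculation at 85% power also gives 19. The first contradicts the printed α/2 quantile and the second contradicts β = 0.10.

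**Step 4: does the recruitment goal still hold?**

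22 / (1 − 0.20) = 27.5, so 28 recruited per group are needed, which is below 35. Conversely, 35 × 0.80 = 28 evaluable per group. Power for 2.2 points at SD 2.25 is then 95.5% (normal) or 94.9% (t). The loss that 35 per group can absorb before falling below requirement is 1 − 19/35 = 46% on the stated figure and 1 − 22/35 = 37% on the corrected one.

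**Step 5: secondary note on 20% and 2.2 points**

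20% of 11 categories is 2.2, and 20% of a 10-point range is 2.0. With 2.0: N = 10.507 × 10.125 / 4.00 = 26.60, so 27 per group (28 by t-test). With 28 evaluable, power is 91.4% (normal) or 90.4% (t).

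**Step 6: sensitivity to the protocol's SD range** (28 evaluable, difference 2.2)

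- SD 1.5: power above 99%
- SD 2.25: about 95%
- SD about 2.5: about 90%
- SD 3.0: about 77% by t-test (78.3% normal), and the formula would require 39.08, so 40 per group

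**The case against.** The strongest reply is that nothing in the design depends on 19. Recruitment is fixed at 70, nobody plans to analyse 19 per group, and the corrected 22 becomes 28 after the drop-out allowance, well inside 35. That stands, and it limits the point to a reporting correction.

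Three stronger readings are tempting, and the protocol does not support them.

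- **That the trial is underpowered.** It is not under its stated assumptions: 28 evaluable per group give about 95% power for 2.2 points, and about 90% even for 2.0. The figure of 28 may itself be cautious. The protocol plans intention-to-treat analysis, continued data collection after withdrawal from treatment, and carrying the last measurement forward, so the number analysed need not fall that far.
- **That the target difference is miscalculated and 27 per group is the true requirement.** The section fixes 2.2 explicitly, calls its expectations arbitrary, and enters 2.2 rather than a percentage in the formula. It never says 20% of the range. The label is loose, but the input is not wrong.
- **That the margin is wrong because SD 3.0 would need 40 per group.** The protocol discloses the range, chooses its midpoint, and nowhere claims 90% power at the upper end. At the lower end, power exceeds 99%.

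It can also be said that 19 may come from a one-sided t-test. That is a plausible origin, but it is an inference. The printed formula is two-sided and no one-sided test is declared anywhere in the article.

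**Conclusion.** The stated 19 per group is wrong by the protocol's own two-sided formula, which gives 22 (23 by t-test). The shortfall is 3 patients per group, or 4 by t-test. At 19 per group, power is about 85% (83.5% by t-test) instead of 90%. This rests only on the printed inputs: α 0.05 two-sided, power 90%, SD 2.25, difference 2.2 and equal allocation.

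The practical effect is that the headroom in 35 per group is overstated, not used up, and the recruitment target need not change.

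The 20% label is a secondary matter of wording. The SD 3.0 result is a sensitivity note and not an error. It does bear on the closing statement about a null result: if the SD were 3.0 and 28 per group were analysed, a true 2.2-point difference would be missed in roughly 23% of trials (100% − 77%).

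**What to change.** 1. Replace 19 with 22 per group (23 if t-based). If a one-sided test was truly used, correct the printed formula and declare the test instead.
2. Keep the goal of 35 per group, and state that after 20% drop-out (28 per group) it gives about 95% power for 2.2 points at SD 2.25.
3. Reconcile the 20% with the 2.2 points: either say that 2.2 is the chosen difference and drop or explain the percentage, or set 2.0 and report 27 per group (28 t-based), with about 90% power at 28 evaluable.
4. Optionally, add that with 28 per group power for 2.2 points falls to about 77% at SD 3.0, and temper the statement on how a null result in 70 patients would be read.

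The cost is a few sentences of rewording. No patients, visits or procedures are added. The only loss is that the stated headroom looks smaller.

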### Experimental intervention

First, we would like to make some general remarks on why we chose to embed mental practice in therapy and not give mental practice as an additional intervention outside of guided practice (f.i. with an audio tape). There is some evidence that mental rehearsal should be combined regularly with the overt movement to increase imagery vividness [17-20]. Next, improving skills seems to depend on continuous practice [2,3,5,21]. Last, we believe that a higher training intensity will not only increase skills but also consolidate the mental practice technique, making the patient more confident that he/she is practicing correctly and thereby increasing compliance and motivating patients to practice unguided.

The experimental intervention period is divided into four phases (fig. 2). In the first sessions, patients will first be familiarised with mental practice-based therapy and educated by their treating therapists as to basic imagery principles and the importance of imagery training on a regular basis (*phase 1*). There is some evidence that patients educated on and familiarised with the technique are more likely to practice in general and to practice correctly by themselves [22-24].

**Figure 2 F2:**
[figure not shown]
Overview of mental practice training phases and their aims. * at least 3 times 10 minutes a day. Preferably, mental practice is combined with physical or occupational therapy or the overt movement at lunch time. Time spend on mental practice unguided can be increased considerable due to compliance/motivation of the patient to practice. Training data are recorded in a personal log (diary) preferably by the patient or assisted by a member of the family or therapist/nurse.

During the next one to two weeks, *phase 2*, they will be taught by their treating therapist how to use the mental practice technique to improve 'drinking from a cup' (occupation therapy) and/or 'walking – with(out) walking aids' (physiotherapy), depending on what they want to improve. The main reason that we chose these two activities is that patients report these activities most frequently, as activities they want to improve when starting rehabilitation. We also wanted two common activities for all patients to practice so that we can standardize the learning process and we will be able to compare results, at the end of the study. Third, 'drinking from a cup' and 'walking' are different kind of tasks; walking is repetitive with timing of different body segments (arm swing, body rotation combined with leg swing), whereas drinking is a 'forward-back movement', where the different parts of the movement seem to follow each other up in time. Perhaps these movements involve different amounts of cortical information. This could imply that certain movements are more suitable to practice mentally for they need more cortical involvement (attention) for a successful performance. Within the speech therapy, mental practice will be used to improve 'swallowing problems' or motor problems due to facial pareses, like 'smiling' symmetrically. We see no direct plausibility to improve aphasia with mental practice and have found no evidence for it in literature.

We will use results from the Structural Dimensional Analysis of Motor Memory (SDA-M) [17,18,20] to determine the basic architecture of specific goal-directed movements and thus to guide the imagery given through identifying inappropriate mental processes. It is for example used to identify weak spots in the sequence of events that should lead to a certain motor performance in sports.

### Control intervention

The *control group *will receive therapy as usual in accordance with the Dutch Guidelines for Stroke Rehabilitation [2,3,21]. To compensate for the unguided imagery training, patients in the control group will be encouraged to do 'homework' as well, primarily practicing tasks that they find difficult. Participants in the control group will also be instructed to use logs.

### Study parameters/endpoints

Measurement dates are at entry in the study (T0 – baseline), after a six weeks intervention period (T1) and six months after entry (T2). Additional information during the course of rehabilitation will be collected, e.g. recurrence of stroke, other intercurrent medical problems, amount of therapy received, used medication. In addition, any deviation from the treatment protocol and any co-intervention during the six months will be recorded.

In the choice of measuring instruments following considerations were taken into account.

• The measuring instruments should have sufficient methodological quality and feasibility recorded in literature and/or be recommended by the National (Dutch) stroke Guidelines;

• If possible, the measuring instrument should be part of the standard assessment in the nursing homes to restrict the additional load on the patient;

• If the quality of a listed measuring instrument has not yet been established the measuring instruments should have evidence from other studies on their potential use in stroke rehabilitation;

• The feasibility will be measured by using semi-structured interviews (process evaluation), recording co-interventions, analysing logs and monitoring therapy content in the experimental group.

The extra load for the participants due to additional clinical testing is approximately 20 minutes at each assessment point.

